#### **4.3 Preoperative evaluation and surgical period**

After completing neoadjuvant treatment, peripheral blood routine, blood biochemistry, stool routine, urine routine, 12-lead electrocardiograms, tumor markers, and coagulation function should be performed to evaluate the efficacy as well as the patients' physical condition. Without clear surgical contraindications and with the patients' consent, surgery will be performed 2–4 weeks later. If disease progresses, radiochemotherapy or salvage surgery is recommended.

- Record the results of peripheral blood routine, blood biochemistry, stool routine, urine routine, 12-lead electrocardiograms, tumor markers, and coagulation tests which are performed 7 days before and after the surgery;

- Retain pathological tissue specimens after surgery;
- Record the reasons for not surgery;
- Record operation time, blood loss, and intraoperative complications (e.g. major bleeding);
- Record postoperative complications and management;
- Record pathological type, number of lymph nodes harvested and metastasis;
- Record postoperative hospital days.

#### 4.4 Adjuvant treatment period

Intervention group: All enrolled patients receive 6 postoperative cycles of apatinib (500 mg orally once daily on days 1 to 21) plus SOX (S-1, 40-60 mg orally twice daily on days 1 to 14; oxaliplatin, 130 mg/m^2 intravenously on day 1) every 3 weeks.

- During adjuvant treatment, peripheral blood routine and blood chemistry are performed on days 1, 7 of cycle 1 and day 1 of cycles 2, 3, 4, 5, and 6;
- Physical examination, ECOG PS assessment, tumor markers, and electrocardiograms are performed on day 1 of each cycle;
- Imaging examination should be performed under the same conditions (layer thickness of scanning, use of contrast agent, etc.) every 3 cycles;
- Discomforts during the treatment should be recorded and graded according to the NCI-CTCAE, version 4.0. If necessary, develop the treatment plan with the department of oncology, and record the reasons for dose adjustment or delay, supportive treatment, and outcomes in the CRF;
- Blood pressure monitoring is performed by the patient himself/herself and recorded in the diary card. Measurement should be done at least 3 times a week during the first 2 cycles. If abnormal, the blood pressure should be monitored daily; otherwise the blood pressure is measured weekly after 2 cycles. At each visit, researchers will measure the blood pressure again. Before measurement, smoking and coffee are not permitted. Take a sitting position. The elbows should be placed at the same level as the heart, and each measurement should be taken on the same side.

#### 4.5 Follow-up period

After the last drug administration, patients enter follow-up period. All patients are followed up with every 3 months during the first 2 years and then every 6 months beyond the third year. The status of each follow-up should be

recorded in the follow-up table.

Assessment of follow-up period: chest X-ray, whole abdominal CT, peripheral blood routine, tumor markers; gastroscopy is recommended to be performed once a year.

Location and time of tumor recurrence or metastasis and cause of death should be recorded in detail.

## **5. Observation of Adverse Events**

### **5.1 Definitions**

Adverse Event (AE): Any adverse medical event that occurs after receiving a drug or treatment, and it is not necessarily related to treatment.

According to regulations, events that occur before and after treatment are both called AEs. Therefore, monitoring of AEs should be performed from entering the trial to the end of the visit.

Severe adverse event (SAE): Any adverse medical event requiring hospitalization, prolonged hospital stay, or causing disability, impaired work capacity, life-threatening complications/death, and congenital malformations.

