### 3.4 Research Flow

Start Date: The date on which the written informed consent is signed

End Date: The last day of the post-treatment period (eg, 30 days after the last drug administration).

The expected treatment duration of this study is 36 months, including 24-month enrollment period. Each participants will be followed up from the Start Date to the End Date, and then for at least 5 years.

If some participant receives a new anti-cancer therapy, monitoring of AEs will be terminated at the beginning of this therapy.

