#### **3.5.2 Safety Assessment**

(1) Surgical safety: including surgical mortality, surgical morbidity (bleeding, anastomotic leakage, wound infection), reoperation rate, length of stay, etc.

(2) Drug safety: including AEs, SAEs, and drug-related AEs (e.g. hypertension, hand-foot syndrome, and proteinuria).

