### **5.3 Recording and Reporting of AEs**

When AEs or SAEs occur during the treatment period, the time of occurrence, clinical manifestations, management, outcomes, and their relation to the study drugs should be recorded in the CRF. Patients with abnormal laboratory tests should be followed up until the results return to normal or to pre-treatment levels. Any SAE should be recorded in the specific tables and reported to the sponsor, ethics committees, Department of Safety Supervision of CFDA, and Department of Health Administration within 24 hours.

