### **● Safety**

These results mainly use description analysis. List all the AEs in this study. List the frequency and percentage of postoperative morbidity, mortality, readmission, and reoperation and the median with range of blood loss, time to food intake, and postoperative hospital days.

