#### 1. General Considerations for Dose Adjustment

- For AEs present at baseline, the dose can be adjusted according to the change in grades. For example, if grade 1 weakness at baseline progresses to grade 2 during treatment, the dose can be adjusted as the presence of a grade 1 toxicity.
- There is no need to reduce the dose or discontinue the treatment with the presence of the toxicities which are unlikely to develop into severe events (such as hair loss, appetite changes, etc.) occur. Additionally, there is no need to reduce the dose or discontinue the treatment with the presence of anemia (non-hemolytic) because it can be improved by transfusion.
- When different grades of toxicities occur simultaneously, dose reduction should be taken according to the most severe of them.
- During treatment, if all study drugs need to be delayed or discontinued for more than six weeks, the patient will withdraw from the study. If only one drug is discontinued, the study still proceeds.
- If a patient develop a grade 3 or higher non-hematological AE, it can be discussed with the sponsor whether to reduce the dose or not.

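### Section 5.1 gives two AE definitions that disagree on events before the first dose, so the all-AE and SAE results have no single onset window.

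*Protocol*

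**What the plan says.** Section 5.1 opens with a post-exposure definition: "Any adverse medical event that occurs after receiving a drug or treatment, and it is not necessarily related to treatment". The next paragraph widens it: "According to regulations, events that occur before and after treatment are both called AEs". From this it concludes that "monitoring of AEs should be performed from entering the trial to the end of the visit". Section 3.4 ties trial entry to consent ("Start Date: The date on which the written informed consent is signed"), and Section 6.1 also starts data collection when the consent form is signed.

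Other places describe a later start. The CRF instruction in Section 5.3 begins "When AEs or SAEs occur during the treatment period" and asks for onset time, management, outcome and relation to study drug. In the flow chart, the adverse-event row is empty in both screening columns, and its first mark is at cycle 1, day 7.

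On reporting, the Safety paragraph of the Statistical Analysis section says "List all the AEs in this study". The outcome definition in Section 3.5.2 reads "2) Drug safety: including AEs, SAEs, and drug-related AEs", so all AEs and all SAEs stand under the drug-safety label beside the drug-related subset. Section 2.2 names toxicity among the secondary endpoints.

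**The concern.** The protocol does not leave the AE start point open. It states two start points that cannot both apply. A site that follows the second sentence of Section 5.1 records an event in the days between consent and first dose as an AE. A site that follows the first sentence, Section 5.3 or the flow chart does not. This is a multicenter study, so the difference can appear as a difference between centers.

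The reporting text does not settle the matter, because it lists every AE without asking when it began and presents the result as drug safety. The trial has a single arm, so no comparator shows how many such events arise without the regimen. Any pre-dose event that gets in is read as part of the regimen's toxicity.

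**Working it through.** The protocol gives no figure to reproduce. The check is to follow one event through each place that bears on it.

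**Test case (hypothetical).** A patient signs consent, has a febrile illness that prolongs the hospital stay, recovers, starts treatment and completes at least one cycle.

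| Place in the protocol | Is the pre-dose illness an AE, or recorded as one? |
|---|---|
| 5.1, first definition | No; nothing has yet been received |
| 5.1, second definition, read with 3.4 | Yes; it precedes treatment but follows trial entry |
| 6.1 data collection window | Inside; the window opens at consent |
| 5.3, CRF recording | No; it is before the treatment period |
| 5.3, SAE reporting | Unclear; the sentence covers any SAE and names no period |
| Flow chart, AE row | No; both screening columns are blank |
| Safety Analysis Set | Patient included; at least one neoadjuvant cycle and safety records are required |
| Statistical Analysis, Safety paragraph | Included if recorded; no onset limit |
| 3.5.2 drug safety | All-AE and SAE components: included if recorded. Drug-related component: unlikely, because relation to drug is judged |

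**What follows.**

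1. The places disagree on one event in one patient, and nothing says which governs.
2. The Safety Analysis Set decides which patients are analysed, not which of their events. It removes people who never received a cycle, but not a pre-dose event in someone who was later treated.
3. The exposed interval is short. Section 4.1 places the earliest screening steps within 2 weeks before treatment starts. The flow chart says 2 weeks before enrollment and puts consent in that column. If enrollment and treatment start are close together, the gap is about 2 weeks at most.
4. The effect per patient can be stated; the total cannot. With the planned 50 patients, and assuming all are in the Safety Analysis Set, one patient counted for an event type only because of a pre-dose event moves that incidence by 1/50 = 2 percentage points. A patient who also has the same type of event on treatment moves it by nothing. The protocol does not say how many patients to expect in the first group.

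**The case against.** The best defence is that separating treatment-emergent events is ordinary SAP work. The SAP is not shown, and a complete listing is not an incidence estimate. Onset time is recorded, so the analyst could split events later. This stands to a degree: the absence of a treatment-emergent rule would not be a finding by itself. It does not answer the conflict within Section 5.1. An SAP can restrict what was recorded, but it cannot restore events that some sites did not record because they followed a different sentence.

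A second defence is that Section 5.3 and the flow chart already point to the treatment period, so in practice few pre-dose events would be captured. That is a fair reason to expect a small effect. It is also one side of the contradiction, not a resolution of it.

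A third is that the wider sentence in Section 5.1 is attributed to regulations and should not simply be struck out. This is accepted: early collection is not the problem, and the remedy below keeps it.

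A reader might also infer that a stable abnormality at screening, such as a raised ALT allowed by the entry limits, would be counted as a liver AE. The protocol does not support that. The wider sentence speaks of events that occur, and an unchanged baseline value is not clearly one. Section 5.3 follows abnormal tests back to normal or to their pre-treatment level. Appendix 5 says "For AEs present at baseline, the dose can be adjusted according to the change in grades". Both take the pre-treatment state as the reference, although Appendix 5 does so for dosing only.

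**Conclusion.** The inconsistency is real and worth correcting, within limits. It concerns events between consent and first dose in patients who go on to treatment. Those events can be counted at some sites and not at others, and can enter the all-AE and SAE results reported as drug safety. The primary endpoint, R0 resection rate, is not touched.

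Two stronger conclusions are tempting and should not be drawn. A reader might infer that findings in people who were never treated enter the drug-safety outcome. The Safety Analysis Set excludes them, although the Safety paragraph does not name that set. A reader might also try to put a number on the inflation by assuming a pre-dose and an on-treatment incidence and combining them. The protocol supplies neither rate. A rate based on abnormal screening values would rest on the reading set aside above, and independence of the two would be doubtful.

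The size is therefore unknown. It is probably small, given the short interval and the sections that point to recording on treatment. This judgement assumes that consent falls within the screening window of about 2 weeks and that relation to drug is judged sensibly for pre-dose events.

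**What to change.** - **Sections 5.1 and 5.3 and the flow chart:** keep collection from consent and state one window in all three. Reword the first definition in Section 5.1 so that it no longer excludes what the second includes. Extend the recording instruction in Section 5.3 to start at consent. Mark the AE row of the flow chart for the time from consent to first dose.
- **Safety paragraph of the Statistical Analysis section:** name the Safety Analysis Set. Report the incidence, by worst grade, of events that start, or worsen from the last pre-dose value, after the first dose of any study drug. List events between consent and first dose separately, so that they stay visible without being attributed to the regimen.
- **Section 3.5.2:** let the AE and SAE components of drug safety refer to that post-first-dose definition.

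The cost is wording in these places and one derivation of onset or worsening against baseline. Onset times and screening values are already collected, so no new assessment is needed.

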### **5.2 Degree of Severity**

Severity of AEs should be evaluated according to the NCI-CTCAE, version 4.0.

### **5.3 Recording and Reporting of AEs**

When AEs or SAEs occur during the treatment period, the time of occurrence, clinical manifestations, management, outcomes, and their relation to the study drugs should be recorded in the CRF. Patients with abnormal laboratory tests should be followed up until the results return to normal or to pre-treatment levels. Any SAE should be recorded in the specific tables and reported to the sponsor, ethics committees, Department of Safety Supervision of CFDA, and Department of Health Administration within 24 hours.

### **5.4 Prevention and Treatment of Risks**

Close attention should be paid to each participant during the treatment period, and management should be done in time when AEs occur.

## **6. Data Collection and Statistical analysis**

### **6.1 Data Collection**

The duration of data collection is from the date when ICF was signed to 30

days after the end of the last drug administration.

Each participants will receive planned visits. Specific data will be recorded at each visit.

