#### **- Secondary Efficacy Measures**

Calculate the pathological/radiologic response rate with 95% CI. The Kaplan-Meier method is used to analyze overall survival (OS) and disease-free survival (DSS), and the differences are assessed with log-rank tests.

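### Section 6.1 ends all data collection 30 days after the last drug dose, which contradicts the planned follow-up of at least 5 years, the OS/DFS analysis and the recording of postoperative complications

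*Protocol*

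**What the plan says.** Section 6.1 (Data Collection) states "The duration of data collection is from the date when ICF was signed to 30" and continues "days after the end of the last drug administration". The sentence covers all data, with no carve-out for survival or surgical outcomes.

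Other sections plan data beyond that point:

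- Section 3.4 uses the same landmark, "End Date: The last day of the post-treatment period (eg, 30 days after the last drug administration", but then has every participant followed "and then for at least 5 years".
- Section 4.5 starts follow-up after the last dose, with visits "every 3 months during the first 2 years and then every 6 months beyond the third year". Status goes into a follow-up table, and the site and timing of relapse and the cause of death are to be documented.
- Section 4.3 says that, once neoadjuvant treatment is complete, "surgery will be performed 2–4 weeks later". It asks for postoperative complications to be recorded and sets no end to that recording.
- The synopsis names DFS and OS as secondary outcomes. The Secondary Efficacy Measures part of the analysis section says "The Kaplan-Meier method is used to analyze overall survival (OS" and adds disease-free survival.
- Section 3.5.2 makes surgical mortality, morbidity and reoperation safety endpoints.

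**The concern.** The section that governs data collection stops before the period that supplies most events for two named secondary endpoints. A site or data manager who follows 6.1 and one who follows 4.5 would deliver different survival data.

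The cut-off is also tied to drug and not to surgery. A patient who starts adjuvant therapy gets a new last dose months later, so the postoperative course is fully covered. A patient who dies after surgery cannot start adjuvant therapy, and one with a major complication is plausibly less likely to. For these patients the last dose is the final neoadjuvant one, and the 30 days are largely used up before or soon after the operation. Under a literal reading, the time observed for surgical mortality, morbidity and reoperation would depend on the outcome itself and would push those rates downward.

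**Working it through.** The plan gives no power or event figure on this point, so there is nothing to reproduce. The check is calendar arithmetic on 6.1 read literally, plus an illustration for survival.

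**Inputs from the protocol.** Window: 30 days after last dose (6.1). Neoadjuvant treatment: 2–5 cycles of 3 weeks, S-1 on days 1–14, apatinib omitted in the last cycle (4.2), so the last preoperative dose is S-1 on day 14. Surgery: 2–4 weeks after completion (4.3). Adjuvant treatment: 6 cycles of 3 weeks, apatinib through day 21 (4.4). Sample size: 50 (synopsis).

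**Assumed.** The gap from surgery to adjuvant therapy is not stated. I take 4–6 weeks, and 3–8 weeks as a wider range.

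**1. Operated, no adjuvant drug.** Postoperative days collected = 30 − (days from last dose to surgery).

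- If completion means the last S-1 dose, surgery falls on day 14–28: 30 − 14 = 16 and 30 − 28 = 2 days.
- If completion means the end of the 21-day cycle, add 21 − 14 = 7 days, so surgery falls on day 21–35: 30 − 21 = 9 and 30 − 35 = −5 days.

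Neither reading gives 30 postoperative days. At the far end of the second, the window closes before surgery.

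**2. Full course.** Weeks from treatment start to closure = neoadjuvant + interval to surgery + assumed gap + adjuvant + 30 days:

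- shortest: 6 + 2 + 4 + 18 + 4.3 = 34.3 weeks
- longest: 15 + 4 + 6 + 18 + 4.3 = 47.3 weeks

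With the wider 3–8 week gap, and surgery counted from the last S-1 dose, the result is 35 + 14 + 21 + 126 + 30 = 226 days to 98 + 28 + 56 + 126 + 30 = 338 days, or 7.4 to 11.1 months at 30.4375 days per month. Section 3.4 plans at least 5 years beyond this point.

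**3. Share of deaths inside the full-course window (illustration).** Assume exponential survival from treatment start, 50 patients all on the full course and no losses. Deaths by month t = 50 × (1 − exp(−h·t)), with h = −ln(S5)/60, where S5 is 5-year OS. The Background quotes 36% (perioperative chemotherapy) and 23% (surgery alone) from a cited trial; 60% is added as an optimistic assumption.

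| 5-year OS | Deaths by 7.4 months | Deaths by 11.1 months | Deaths by 60 months | Share inside window |
|---|---|---|---|---|
| 23% | 8.3 | 11.9 | 38.5 | 22–31% |
| 36% | 5.9 | 8.6 | 32.0 | 18–27% |
| 60% | 3.1 | 4.5 | 20.0 | 15–23% |

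Across these assumptions, 15–31% of the 5-year deaths fall inside the window and 69–85% outside it.

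**4. Visit schedule.** Read word for word, 4.5 places 3-monthly visits in months 0–24 and 6-monthly visits after month 36. Months 24–36 then have no stated schedule.

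**The case against.** The best defence is to read the sections together. On that view 6.1 describes the phase from consent to the End Date of 3.4, and survival comes from the follow-up table of 4.5. Section 6.1 itself adds that data are recorded at planned visits, and follow-up visits are planned. Section 4.3 sets no cut-off for complications, the flow chart records adverse events in the week after surgery whether or not drug is being given, and 4.4 plans adjuvant therapy for everyone. The length of a postoperative interval may also be left to an SAP.

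Much of this stands. A reader might infer from 6.1 that DFS and OS data are lost or cannot be estimated. The documents do not support that: 3.4 and 4.5 expressly plan these data, and even a literal cut-off would leave estimates for roughly the first 7–11 months. A reader might also infer that R0 status could fall outside the window. That requires no adjuvant drug, the interval to surgery counted from the end of the cycle and close to its 4-week maximum, and 6.1 overriding 4.3, which governs surgery and retention of the specimen.

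A reader might further infer that the short window applies to every operated patient, because the synopsis lists surgery among the criteria for stopping treatment. Section 3.2.4 does not list it and 4.4 continues treatment after surgery. Those passages must be reconciled, but they do not establish that reading.

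What does not stand is that the joint reading settles the matter. Section 6.1 is unqualified and nothing says which section prevails. The flow-chart column covers only one week after surgery. An SAP can define an interval, but it cannot recover data that a site stopped collecting under the protocol.

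**Conclusion.** Section 6.1 is wrong as written: it contradicts sections 3.4, 4.3 and 4.5 and the OS/DFS analysis. If followed literally, it closes at about 34–47 weeks for a full-course patient (given the assumed 4–6 week gap), before most survival events. It leaves 2–16 postoperative days, or −5 to 9 on the other reading of completion, for an operated patient who starts no adjuvant drug.

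The direction of the surgical-safety bias is clear, towards rates that are too low. Its size cannot be estimated, because the documents give neither the proportion of operated patients without adjuvant therapy nor a complication rate. The share of deaths captured rests on exponential survival and borrowed survival rates and is only illustrative.

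The effect is confined to secondary endpoints. The year-3 visit gap is minor: the phrase most naturally means from the third year onward, so it is a wording ambiguity and not evidence that relapses would be missed.

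**What to change.** Reword 6.1 in three parts:

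1. The limit of 30 days after the last dose applies only to the collection of drug-related adverse events.
2. DFS and OS data are collected from consent through the follow-up of sections 3.4 and 4.5.
3. Surgical mortality, morbidity and reoperation are collected for every operated patient over one fixed interval counted from the date of surgery, whether or not further drug is given. The protocol should state the length.

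In 4.5, reword the visit schedule so that months 24–36 are unambiguously covered.

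The cost is protocol wording, plus case report form pages that the follow-up of at least 5 years already requires. Sample size and the planned analyses do not change.
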